## Background

Intrathoracic anastomotic leaks occur in up to 20% after Ivor Lewis esophagectomy. This complication is associated with a prolonged hospital stay and increased postoperative mortality and therefore one of the most feared complications in visceral surgery [1–4]. During the last years, there has been a controversial debate about the optimal treatment strategy of anastomotic leaks ranging from conservative over interventional endoscopic to surgical approaches [4–6]. While early anastomotic leaks, particularly in the presence of sepsis, as well as extended conduit necrosis still remain a recommended indication for surgical revision, growing expertise suggests endoscopic treatment in the case of leaks, which are defined as localized retentions connected to the site of anastomotic insufficiency [7–10]. The current gold standard in the endoscopic management of anastomotic leaks seems to be the usage of self-expanding metal stents (SEMS), with success rates of approximately 70–81%. Endoscopic vacuum therapy (EVT) represents a newer alternative that has been introduced by Wedemeyer and colleagues in 2008. Since then, an increasing number of patients has been treated with this method showing promising results in retrospective studies: The healing rates range between 67 and 100% [11–18]. Both treatment strategies present advantages and drawbacks: While SEMS provide a complete seal of the leak and maintain the esophageal passage for oral intake, they might induce ischemia and require the placement of additional drainages in some of the patients. Stent migration is a common problem calling for re-interventions. Endoscopic vacuum therapy offers continuous fluid collection facilitating the granulation process and reducing bacterial proliferation, but needs to be changed every 2–5 days, requires a trans-nasal suction drainage, and forbids oral nutrition [19, 20].

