### Follow-up

Following the primary endoscopic intervention, the patient will be treated according to the clinic’s standard operating procedures. If the patient’s clinical status does not improve within 72 h, endoscopic reevaluation and/or another CT scan will be performed. In case of new fluid collections, a drainage will be inserted. If endoscopy shows necrosis or severe ischemia of the interponate or a significant increase of the anastomotic leak size, a surgical revision will be evaluated by the treating physician taking into account the patient’s clinical status.

During the hospital stay, the following data are determined on days 3, 7, 14, 21, and 28 and then weekly (±1 day) after the diagnosis of anastomotic leakage as illustrated in Table 1: vital signs, SOFA score, duration of ventilation, leukocytes, CRP, and procalcitonin value, if applicable [22]. All relevant endoscopic, surgical, and non-surgical complications throughout the hospital stay including postoperative death will be documented in the CRF (Table 1). Follow-up examinations are performed 3 and 6 months (±14 days) after inclusion (Table 1). In addition to assessing the quality of life and the clinical status, the following details are documented on follow-up visits: body weight, Karnofsky index, presence of dysphagia or a symptomatic stenosis, oncologic status (relapse/remission), and tumor-specific therapy, if applicable. The recurrence rate and mortality including the cause of death will be documented beyond the last study visit contacting the treating physician or the patient.

**Table 1 Tab1:** Trial events according to treatment and follow-up plan

		Intervention phase		Follow-up (time after informed consent)		
Trial checkpoint	Screening	Prior to treatment	Hospital stay after inclusion	3 months (± 14 days)	6 months (± 14 days)	12 months (± 14 days)
**Informed consent**	X					
**Inclusion/exclusion criteria**	X					
**Medical history, physical examination, vital signs**	X^a^	X	X^b^	X	X	X
**Diagnostic upper GI endoscopy**		X				
**CT scan**		X	(X)		x	
**ECG**	X					
**Laboratory tests**	X	X	X^b^	X	X	X
**Operative report**		X	X			
**Postoperative complications, treatment failure**		X	X			
**SOFA score**		X	X^b^			
**QoL questionnaire**	X		X^c^	X	X	X
**Treatment costs**			X			
**Monitoring of SAE**		X (from randomization to discharge from hospital + 30 days)				
**Overall survival**		X				

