#### Secondary effect measures

Cure rate of patients within 44 days postoperatively. Cure is defined as follows:
○ No leak can be detected clinically, endoscopically, and/or radiologically *or*○ Patients are able to be discharged from the hospital despite persistent leakage (treated with SEMS or drainages), once they are in a clinically stable state without signs of acute inflammation and tolerate oral food intake.○ In case of death within 44 days postoperatively and persistent leak, patients are classified as “not cured.”Period of hospitalization, defined as the time in days from the day of surgery (day 0) until discharge from the hospital to ambulant or for follow-up treatment (except early rehabilitation or neurological rehabilitation)Rate of and reasons for treatment failure, defined as a necessary change of the treatment strategy or postoperative deaths, that are directly or indirectly associated with the anastomotic leakRate and type of surgical revisions with indication of the reasonsGeneral complications (surgical and non-surgical complications) and treatment-specific complications such as stent dislocations, which will be classified according to the Clavien-Dindo classification and the Comprehensive Complication Index [22]Mortality, defined as postoperative death within 30 and 90 days (30-day and 90-day mortality) and during the hospitalization period. In addition, we determined whether the patients died as a direct or indirect result of the insufficiency.Duration of intensive care treatment (starting from diagnosis of the anastomotic leak)Influence of treatment on possible sepsis, as measured by the SOFA score [26, 27]Ventilation time (measured ventilation time in hours from inclusion to extubation or continuously spontaneously breathing tracheostomized patients, respectively)Duration of therapy (from the time of inclusion until the removal of the last drainage or stent)Number of endoscopies throughout the trial with indication of number of SEMS or vacuum system replacements and/or revisionsDuration of healing (from the day of inclusion until no leakage can be detected endoscopically)Time from inclusion to oral food intakeTreatment costs (inpatient and outpatient)Occurrence of symptomatic stenosis with indication of chosen specific treatment

Secondary outcome measures will be registered up to 1 year after inclusion.

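### The cure definition has no durability rule: a patient discharged with an open leak who relapses before day 44 can still be scored as cured

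*Protocol article*

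**What the plan says.** Under Secondary effect measures, the protocol article sets the endpoint as "Cure rate of patients within 44 days postoperatively" and then defines cure in three items.

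- First route: "No leak can be detected clinically, endoscopically, and/or radiologically".
- Second route, offered as an alternative to the first: "Patients are able to be discharged from the hospital despite persistent leakage (treated with SEMS or drainages), once they are in a clinically stable state". Its conditions are tied to the point of discharge: "once they are in a clinically stable state without signs of acute inflammation and tolerate oral food intake".
- A rule for death, which gives the class not cured and begins "In case of death within 44 days postoperatively and persistent leak, patients are classified as".

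Treatment failure is a separate secondary endpoint, "Rate of and reasons for treatment failure, defined as a necessary change of the treatment strategy or postoperative deaths", limited to what is directly or indirectly linked to the leak. The cure definition does not refer to it.

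On timing, the Follow-up section says "Follow-up examinations are performed 3 and 6 months (±14 days) after inclusion". Effect evaluation adds a quality-of-life questionnaire at 1 month after randomization. No examination is set for day 44.

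**The concern.** The second route certifies a patient at one moment, with the leak still open. A good deal can happen between that discharge and day 44: the stent may move, infection may return, a new drain may be needed. The Background itself says "Stent migration is a common problem calling for re-interventions". The definition gives a rule for one later event, death with a persistent leak, and none for relapse in a patient who survives. It also does not say whether cure means a criterion met at some time up to day 44 or a state present on day 44.

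The abstract names healing rate first among the important secondary endpoints, and the trial exists to find suitable endpoints and to allow a sample size calculation for a larger trial. The article does not say that the cure rate will be the endpoint for that calculation, but it is an obvious candidate. If relapses count as cures, the rate carried forward is too high, and possibly more so in one arm than in the other.

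**Working it through.** **Inputs.** 40 patients (Patients section), allocated 1:1 (Randomization), so 20 per arm. Cure window: 44 days from surgery (Secondary effect measures). Eligible leaks: later than 48 hours and up to 4 weeks after surgery (Exclusion criteria). Stent removal or replacement: 21 days, plus or minus 2 (Control group). SAE monitoring: from randomization to discharge plus 30 days (Table 1).

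**The plan's own figure.** The only computed design figure is the detectable standardized effect of 0.909 (Statistical analysis). A two-sample t-test with 20 per arm, two-sided 5% level and power 0.8 gives 0.9091, so it is reproduced and confirms 20 per arm. It is not tied to the cure rate, for which the plan states no figure.

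**The definition applied to patient paths.**

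1. Discharged stable with an open leak, still stable on day 44: cured on any reading.
2. Discharged stable with an open leak, relapses before day 44, alive: the second route was met and no item reverses it. Cured if a criterion need only be met at some time; not cured if status on day 44 is meant. The text does not choose.
3. Discharged stable with an open leak, dies by day 44 with the leak persisting: the death item assigns not cured.
4. Leak no longer detectable, then reopens before day 44, alive: the same gap as path 2, through the first route.

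**Size per patient.** One reclassified patient changes an arm's rate by 1/20 = 0.05, or 5 percentage points; for example 15/20 = 75% becomes 14/20 = 70%. For scale, assume true rates of 75% with stents and 90% with EVT, which lie inside the ranges quoted in the Background (70–81% and 67–100%). The standard error of the difference is then √(0.75 × 0.25/20 + 0.90 × 0.10/20) = √(0.009375 + 0.0045) = 0.118. One patient is 0.05/0.118 = 0.42 of a standard error. The number of path 2 patients cannot be derived from the documents.

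**Direction.** The second route requires oral intake. By the Background, a stent keeps the passage open for oral intake, while EVT rules out oral nutrition. A patient can therefore qualify with a stent in place but not with a sponge in place. However, the second route also covers drainages, image-guided drains are used in both arms (Image-guided drainage insertion), and EVT may end once the cavity is lined with granulation tissue, without full closure (Intervention group). An EVT patient can thus finish sponge therapy, eat and go home with a drain. The asymmetry is partial.

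**Can status at day 44 be derived without a new visit?** SAE monitoring reaches day 44 if discharge day + 30 ≥ 44, that is, for discharge on day 14 or later. A discharge on day 10 would be covered to day 40, 4 days short. Endoscopies with replacements and revisions, surgical revisions and complications are recorded as well, and secondary outcomes are registered up to 1 year.

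**Scheduled stent work.** 44 − 21 = 23, so for a stent placed by day 23 the nominal removal or replacement falls within the window. A status rule must not read that planned procedure as a relapse.

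**The case against.** The strongest reply is that this is a condensed article. A full protocol is available on demand and a SAP is to be finalized before the first comparative analysis; assessment time and handling of relapse often sit there. It is also fair that the article never says cure is kept once reached. A reader might infer that rule, and it is the natural reading, but the wording only says within 44 days. What remains is that the article prints an operational definition with one explicit reversal. Followed as written, it lets a living relapsed patient count as cured, which goes beyond a detail left for later.

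Second, relapse is not lost from the report. Treatment failure, surgical revisions, stent dislocations, numbers of endoscopies and duration of healing are all separate outcomes, and a relapsed patient would normally appear in at least one. That stands, but none of them corrects the cure rate.

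Third, a reader might infer that a patient discharged with an open leak who then dies with it before day 44 is both cured and not cured. The documents do not support this. The death item sits inside the same definition and is the more specific rule, so it gives one class. At most, its precedence could be stated outright.

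Fourth, the endpoint is secondary, in an exploratory pilot whose p-values are descriptive. This limits the weight of the point.

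**Conclusion.** The point holds as a gap in the definition. Cure through discharge with an open leak needs no durability to day 44, and only death with a persistent leak takes it away. Each patient who relapses after such a discharge and is still scored as cured overstates that arm's rate by 5 percentage points at 20 per arm. Any net error probably leans towards SEMS, but only in part, since EVT patients discharged with drains can also qualify.

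No total bias can be given. A reader might be tempted to use the complement of the quoted stent success, 100 − 81 = 19% to 100 − 70 = 30%, as a relapse rate. That figure is failure among all stented patients, not relapse among those already stable, eating and discharged. The share discharged with an open leak is not in the documents either.

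The conclusion rests on the printed definition and on 20 patients per arm. It should be corrected before any comparative analysis, particularly because the trial is open-label, but it does not touch the primary endpoint.

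**What to change.** State in the endpoint definition and the SAP that cure is status at day 44 after surgery: one of the two cure criteria was met by then, and from that time to day 44 no leak-related readmission, unplanned re-intervention, new drainage or re-leak was recorded. Add two clarifications:

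- The scheduled removal or exchange of a stent does not count as relapse.
- Death within 44 days with a persistent leak is not cured, whatever discharge came before it.

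Derive the status from recorded events, not from a new day-44 examination: SAEs to discharge plus 30 days, endoscopies, revisions and complications. For the few patients who might leave before day 14, use the endoscopy, revision and complication records and ask about events since discharge at the 3-month visit. It would help to report, by arm, how many cures came through each route.

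The cost is a few sentences and one derived variable. The downside is a slightly lower cure rate. No visit, treatment or clinical rule changes.

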#### Intervention group (EVT)

Before the endoscopic placement of the vacuum therapy system, a triple lumen nasojejunal feeding tube is inserted for gastric decompression and to ensure intestinal feeding throughout the duration of the EVT.

The sponge system can be either positioned inside the esophageal lumen (endoluminal position) or into the extraluminal cavity adjacent to the anastomotic leak (extraluminal position). Anastomotic leaks without an accessible extraluminal cavity will be treated by endoluminal sponge placement whereas anastomotic leaks with larger cavities are treated by inserting a manually customized sponge into the cavity. The sponge system will be placed using an overtube and a pusher. Hereafter, the sponge position will be controlled endoscopically and may be adjusted using a forceps. Then the drainage tube is placed via the nasal cavity and secured with adhesive strips or a nasal tube retaining system (e.g., AMT Bridle™, Applied Medical Technology, USA). Subsequently, the drainage tube will be connected to an electronic vacuum pump with a defined continuous suction (e.g., VivanoTec®, Hartmann AG, Germany). Since there is no data concerning the selection of the ideal suction power for EVT, we decided to use a suction power of 125 mmHg, which we have established as a standard in our center in Cologne and Hamburg since 2010. The system exchange or removal is scheduled 3–5 days after the initial placement. To ensure an atraumatic removal of the sponge system, the drainage tube is disconnected from the vacuum pump and 40 ml of saline solution is injected into the tube to wet the sponge and thus facilitate removal. The EVT may be terminated either after full closure of the leak or complete lining of the cavity with granulation tissue. Dislocation or migration of the sponge system is classified as complications.

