#### Control group (SEMS)

Stents used in this study must be self-expanding, partially covered metal stents (CE certified - CE0197). The product will be narrowed down to a few models, but the final decision regarding the stent type and size will be left up to the endoscopist. The stent may be secured in its position by using clips or endoscopic suturing techniques. To achieve optimal coverage and seal of the leak, the flare ends of the stent need to be proximal and distal to the leak. In case of stent dislocation or migration, the stent may be repositioned and fixed or replaced by another model or size with better adjustment. This scenario will be documented as a complication. After successful stent placement, a triple lumen nasojejunal feeding tube suitable for intestinal feeding and gastric decompression is inserted. The stent will be removed or replaced after 21 days (±2 days).

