During each intervention and every study visit during the complete course of the intervention and follow-up, specific complications potentially related to the intervention are documented. AEs and SAEs are collected, and relations to the study intervention interpreted and compared between the two groups and the results published.

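### Scheduled endoscopy is far more frequent under EVT than under SEMS, so the secondary between-arm comparison of device complications is open to ascertainment bias for clinically silent findings

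*Protocol article*

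**What the plan says.** All references are to the protocol article.

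- **When complications are recorded.** Secondary effect measures: "During each intervention and every study visit during the complete course of the intervention and follow-up, specific complications potentially related to the intervention are documented". The same section says that adverse events are compared between the groups. It lists treatment-specific complications as a secondary endpoint, graded by Clavien-Dindo and the Comprehensive Complication Index.
- **EVT looks.** Intervention group (EVT): "The system exchange or removal is scheduled 3–5 days after the initial placement". The Background says of the method in general that it "needs to be changed every 2–5 days".
- **SEMS looks.** Control group (SEMS): "The stent will be removed or replaced after 21 days (±2 days").
- **What counts.** For EVT: "Dislocation or migration of the sponge system is classified as complications". For a dislocated or migrated stent: "This scenario will be documented as a complication". Neither sentence requires symptoms.
- **Provisions shared by both arms.** Follow-up: "During the hospital stay, the following data are determined on days 3, 7, 14, 21, and 28 and then weekly (±1 day"). The items listed are vital signs, SOFA score, ventilation and laboratory values. Relevant complications of the hospital stay go into the CRF. In addition: "If the patient’s clinical status does not improve within 72 h, endoscopic reevaluation and/or another CT scan will be performed".
- **Table 1.** Diagnostic endoscopy appears only before treatment, and the in-hospital CT is in parentheses.

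The Discussion acknowledges that SEMS involves few endoscopies and EVT many, but only when explaining the choice of primary endpoint.

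**The concern.** An event that causes no symptoms is recorded only if someone looks. The two arms are looked at on very different schedules, and the looking is part of the treatment. A sponge found displaced at a planned exchange is a recorded complication. A stent that shifts without symptoms is recorded only at removal, and not at all if it is no longer displaced by then. The Background names migration and ischaemia as drawbacks of stents, so the risks tied to one arm are the ones inspected least often.

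At stake is a named secondary safety comparison. The trial's stated purpose is to define outcome measures and sample size for a larger trial, so a contrast that partly reflects the number of looks would be carried forward.

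**Working it through.** **Plan's own figures.** The article gives no complication rate and no share of events missed between endoscopies. Its only power figure, a detectable effect of 0.909 with 20 per group (Statistical analysis), reproduces as 0.9091 by the two-sided noncentral t. This point does not depend on it.

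**Step 1: scheduled looks.** Inputs are the 3–5 day EVT interval, assumed to repeat, and stent removal at 21 ± 2 days. Looks = whole part of (horizon ÷ interval).

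| Horizon | EVT, 5-day | EVT, 3-day | SEMS |
|---|---|---|---|
| Day 18 | 18/5 → 3 | 18/3 → 6 | 0 (earliest 21 − 2 = day 19) |
| Day 21 | 21/5 → 4 | 21/3 → 7 | 0–1 |

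The EVT counts apply only while therapy continues; the article gives no duration. By day 18 both arms also have three shared visits (days 3, 7, 14), none with endoscopy listed.

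**Step 2: what the shared provisions can see.** The visits record clinical and laboratory status. The 72-hour rule is triggered by failure to improve. Both can reveal a manifest event, but neither is designed to reveal a silent one. The cure definition also allows discharge with a stent in place. The in-hospital schedule then ends, although Table 1 continues SAE monitoring for 30 days after discharge.

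**Step 3: how far silent findings could distort the contrast.** Assumptions, not from the document: equal true risk, a 5% chance of a new silent finding in each interval between EVT looks, independence, and EVT lasting about 21 days.

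- EVT, at least one recorded finding: 1 − 0.95^4 = 0.185 (5-day) to 1 − 0.95^7 = 0.302 (3-day).
- SEMS with one look at removal, if findings persist: the same 0.185 to 0.302. The gap is 0, and the events are merely found late.
- SEMS with one look at removal, if findings resolve within an interval: only the last interval is visible, 0.05. The gap is 13.5 to about 25 points.
- At 10% per interval: EVT 1 − 0.90^4 = 0.344 to 1 − 0.90^7 = 0.522. The gap is 0 if findings persist, and 24 to 42 points against 0.10 if they resolve.
- With only two EVT exchanges: 1 − 0.95^2 = 0.098, against 0.05 for transient findings.

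**Step 4: effect on a test with 20 per arm.** Assumed true rate 30% in both arms, EVT fully detected, Fisher's exact test at 5%.

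| SEMS events detected | Spurious difference | Probability of p < 0.05 |
|---|---|---|
| 100% | 0 points | 2.5% |
| 90% | 30 − 27 = 3 points | 2.7% |
| 70% | 30 − 21 = 9 points | 5.4% |
| 50% | 30 − 15 = 15 points | 12.4% |

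With a 40% true rate and half detected, the difference is 20 points and the probability 19.2%.

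**The case against.** A reader might infer that device complications are documented only at interventions, that stents go uninspected until about day 19, and that the comparison is therefore biased against EVT. The document does not support that.

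- Documentation also takes place at every study visit, and in-hospital complications are captured in both arms.
- Day 19 is the earliest *scheduled* stent endoscopy. The 72-hour rule allows endoscopy or CT earlier in either arm, and the SEMS section provides for a migrated stent to be repositioned or replaced.
- Giving one look after 21 stent-days the same yield as one look after 3–5 sponge-days builds the gap into the model. Step 3 shows that it vanishes when findings persist.
- Repeated sponge placement creates repeated real opportunities for dislocation. A higher EVT count from that source is a treatment effect.
- Only dislocation and migration are expressly classed as complications; the article does not say that ischaemia or leak enlargement is counted at each exchange.
- Severity grading and the recorded number of endoscopies already help interpretation.

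All of this stands and limits the claim. None of it reaches a silent finding between scheduled looks.

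It can also be said that an article leaves such detail to the SAP and CRF, and that the endoscopy documentation form (Fig. 2) is not shown. That is fair for the analysis split. The mode of detection, however, has to be recorded when the event occurs. The SAP is to be finalised on pooled data, and by then a missing field may not be recoverable.

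**Conclusion.** The point holds as a risk, not as a demonstrated bias. Scheduled endoscopic inspection differs by arm, dislocation or migration counts in both arms whether or not it is symptomatic, and the shared provisions cover manifest events only. The comparison of endoscopically detected device complications is thus open to ascertainment bias, mainly for silent findings that are transient or repeated. A persisting stent migration would be found late rather than missed.

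The likely direction is under-recording in SEMS. The size cannot be derived from the document: the illustrations run from no gap to a large one, depending on assumed rates and persistence. The conclusion assumes that EVT exchanges repeat at about the stated interval, which the Background supports but the EVT section states only for the first exchange.

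Severity is minor. The endpoint is secondary, p-values are declared descriptive, and the Discussion says the trial is too small to establish superiority. The case does not extend to the primary quality-of-life endpoint, which patients report themselves.

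**What to change.** Before recruitment starts (Trial status: not yet recruiting):

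1. Add one CRF field per device complication for how it was detected: clinically manifest, or found only at a scheduled exchange or removal.
2. Keep the comparison of all complications.
3. Add a per-patient between-arm comparison of clinically manifest events over one fixed window from randomisation. Ascertain them in the same way in both arms, including in patients already discharged. Define manifest by symptoms or clinical consequence, in advance, because the trial is unblinded.
4. Do not define it by whether an intervention was unscheduled. A displaced sponge can be dealt with at the next planned exchange, whereas a displaced stent found early needs an extra procedure, so that rule would tilt the comparison against SEMS.
5. List findings made only at scheduled endoscopy separately by arm, beside the number of endoscopies that is already a secondary endpoint.

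The cost is one CRF field, a few lines of protocol or SAP wording, and the same questions put to discharged patients. No endoscopy is added and no treatment rule changes. The drawback is that fewer events enter the manifest-only comparison, which makes it less precise.
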